#### Data analyses

The independent researchers performing the biochemical tests, assessing the clinical outcomes, and analyzing the data will be kept blinded to the patients’ identities and grouping.

Continuous indicators are described as means, standard deviation, medians, and interquartile ranges, while classification variables are reported as absolute values and percentages. The following aspects should be analyzed at the end of the trial: the actual number of participants in the two groups, dropped and excluded cases, baseline characteristics, compliance, efficacy, and safety. To insure the comparability between groups, baseline comparisons, including the indicators of demographic characteristics, clinical characteristics, biochemical variables, medical history, and medication history (Tables 2 and 3), were performed according to the data features by independent *t* test, chi-squared test, or Fisher’s exact test.

**Table 2 Tab2:** List of baseline characteristics of participants

Category	Items
Demographic characteristics	Age
	Sex
Clinical characteristics	Known duration of diabetes
	CKD stage
	Body mass index (height and weight)
	Blood pressure
Biochemical variables	eGFR, Scr
	UACR, 24 h UTP
	TC, TG, HDL-C, LDL-C
	ALT, AST, ALP, TBIL, GGT
	PT, APTT, FIB
	Blood glucose
	Glycated hemoglobin
Medical history	Hypertension
	Hyperlipidemia
	Coronary heart disease
	Congestive heart disease
	Stroke
	Peripheral vascular disease
	Others
Medication history	Drug name
	Drug dose
	Beginning drug use date
TCM evaluation scores	Details are listed in Table 3

**Table 3 Tab3:** Traditional Chinese medicine (TCM) symptom assessment survey and evaluation standard

Signs/symptoms		Score				Scores
		Normal: 0	Mild: 2	Moderate: 4	Severe: 6	
Primary signs/symptoms	Dry mouth and throat	None	Decreased saliva production	Moderate thirst relieved by drinking fluids	Severe thirst with constant need to drink fluids	
	Fatigue	None	Cannot sustain heavy work	Can manage mild intensity work	Can only perform daily activities	
Secondary signs/symptoms	Prone to be hungry and eat more	None	Easy to be hungry	Easy to be hungry and unbearable hunger	Unbearable hunger and hypoglycemia	
	Shortness of breath	None	Shortness of breath after mild activity	Shortness of breath after moderate activity	Unable to talk or catch breath even without activity	

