	Heat sensation in chest, palms, and soles	None	Heat sensation in palms and soles at night	Moderate heat sensation in chest, palms and soles	Severe heat sensation in chest, palms, and soles and desire to expose body	
	Fixed pain in the chest, lower back, or limbs	None	Occasional and relieved spontaneously within half an hour	Less than three hours a day, relieved by common drugs	Continuously fixed pain, relieved only by painkillers	
	Numbness of the limbs	None	Tips of hands and feet	Hands and feet	Limbs	
Tongue and pulse	Tongue	Dark red tongue with less fluid coating; others (description):				
	Pulse	Weak and thin pulse; others (description):				

Manifestation of tongue and pulse is only for reference without being calculated in the scores

Evaluation standard of total effective rate of TCM syndrome scale score

(1) Clinical recovery: the clinical symptoms and signs disappear or basically disappear, and syndrome scores are reduced by ≥ 95%

(2) Significantly effective: the clinical symptoms and signs are significantly improved, and syndrome scores are reduced by ≥ 70%

(3) Effective: the clinical symptoms and signs are improved, and syndrome scores are reduced by ≥ 30%

(4) Invalid: the clinical symptoms and signs are not improved, or even worsened, and syndrome scores are reduced by less than 30%

The calculation formula (Nimodipine method) is as follows: [(scores before treatment − scores after treatment) ÷ scores before treatment] × 100%

Total effective rate = (clinical recovery + significantly effective + effective) number of cases/total number of cases × 100%

The total effective rate of the KLX group and the control group after treatment is calculated and compared

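### Table 3: the score-2 and score-4 anchors of the shortness-of-breath item are in the wrong order, so some changes in breathlessness are scored in the wrong direction or by the wrong amount

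*Protocol article*

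**What the plan says.** Table 3 (protocol article, section Data analyses) prints the TCM symptom scale with four columns: "Normal: 0 Mild: 2 Moderate: 4 Severe: 6". A higher score is worse. The shortness-of-breath row has these non-zero anchors:

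- score 2: "Shortness of breath after mild activity"
- score 4: "Shortness of breath after moderate activity"
- score 6: "Unable to talk or catch breath even without activity"

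Fatigue is the other row graded by exertion. It gives 2 to "Cannot sustain heavy work" and 6 to "Can only perform daily activities".

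Seven symptom rows are scored; tongue and pulse are recorded but not counted. Response is the percentage fall from the pre-treatment score, and the lowest responder grade reads "3) Effective: the clinical symptoms and signs are improved, and syndrome scores are reduced by ≥ 30" (per cent). The total effective rate is the share of patients at that grade or better. The Secondary outcomes section lists it at weeks 4, 12 and 24 and at months 6 and 12.

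**The concern.** A person who becomes breathless on mild exertion is worse off than one who becomes breathless only on moderate exertion, yet the table gives the worse state the lower score. The words mild and moderate appear to describe the activity in this row, while the column headings use them for the symptom.

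The item enters a ratio in which the baseline score is both part of the numerator and the whole denominator. A wrong item score can therefore distort the percentage reduction twice, and a patient can be placed in the wrong response category. This is a scoring rule that the article states in full, not a detail left to another document.

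**Working it through.** **Inputs.** Anchors, score columns, formula and 30% cut-off: Table 3. Symptom entry rule (the primary symptoms plus at least two secondary ones): Inclusion criteria. The plan states no figure to reproduce here.

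**1. Order of the anchors.** Score 6 is breathlessness with no activity, so within this row less exertion means worse. The consistent order is none (0), on moderate activity (2), on mild activity (4), without activity (6). The fatigue row runs this way, with heavy work lost first, and the other five items also rise with severity. In the breathlessness row, 0 and 6 are in place; only 2 and 4 are exchanged.

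**2. All six improving changes** (item score after minus before):

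| Change | Printed | Ordered |
|---|---|---|
| mild activity → moderate activity | 4 − 2 = +2 | 2 − 4 = −2 |
| mild activity → none | −2 | −4 |
| moderate activity → none | −4 | −2 |
| no activity → mild activity | −4 | −2 |
| no activity → moderate activity | −2 | −4 |
| no activity → none | −6 | −6 |

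One has the wrong sign, four have the right sign but are wrong by 2 points, and one is unaffected.

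**3. The wrong-signed step on its own.** Let R be the sum of the other six items, unchanged. With both primary symptoms and one further secondary symptom at least mild, R ≥ 2 + 2 + 2 = 6.

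- Improvement: printed reduction −2/(R + 2); ordered 2/(R + 4).
- Deterioration: printed 2/(R + 4); ordered −2/(R + 2).

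The largest reduction under either scoring is 2/(6 + 4) = 20%, below 30%. At a printed baseline of 10:

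- improvement: printed 10 → 12 = −20%; ordered 12 → 10 = +16.7%
- deterioration: printed 10 → 8 = +20%; ordered 8 → 10 = −25%

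All four are non-responses.

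**4. The step combined with changes in other items.**

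| Other items | Breathlessness | Printed | Ordered |
|---|---|---|---|
| 8 → 6 | improves, mild to moderate activity | 10 → 10 = 0% | 12 → 8 = 33% |
| 10 → 6 | improves, mild to moderate activity | 12 → 10 = 16.7% | 14 → 8 = 42.9% |
| 6 → 4 | worsens, moderate to mild activity | 10 → 6 = 40% | 8 → 8 = 0% |

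In the first two rows the printed scoring misses a response; in the third it credits a fall that the ordered scoring does not show.

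**5. Illustration of frequency.** The documents give no score distributions, so these are assumed: item levels uniform, both primary and at least two secondary symptoms present, and each item improving one level with probability 0.3, 0.5 or 0.7.

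| Probability | Wrong side of 30% | Rate, printed | Rate, ordered |
|---|---|---|---|
| 0.3 | 5.9% | 12.3% | 10.1% |
| 0.5 | 13.1% | 36.9% | 36.0% |
| 0.7 | 15.6% | 66.4% | 70.5% |

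Errors in the two directions largely offset, so the net shift in the rate is between about −4 and +2 percentage points.

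**The case against.** The case for leaving this alone has several parts.

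- **Probably a translation slip.** Raters may have scored by the mild, moderate and severe headings, in which case the trial data are sound. This is possible, and the article cannot settle it. A reader might infer that patients have already been mis-scored; the document does not show that.
- **The item is not reversed as a whole.** This stands. A reader might infer that improvement generally raises the score, but that is true of one improving change in six.
- **The step cannot create or remove a responder alone.** This also stands. A reader who sets a 4-point discrepancy against a baseline of 10 might infer a crossing of the 30% line. That overlooks that correcting the item also changes the baseline, and step 3 of the working shows that neither scoring exceeds 20%.
- **Little weight in the trial.** It is one of seven items, worth a 2-point error out of a possible 7 × 6 = 42 at each assessment, in one secondary outcome. The rule is the same in both arms and assessors are blinded. All of this stands: the harm is misclassification, and nothing shows that it favours an arm.
- **The responder grade also requires symptoms to have improved.** This may stop some deteriorating patients from being counted. The article gives no separate measure of it, however, so the score is the only quantified test, and the condition does nothing for improvements that are missed.
- **Recoding could damage good data.** This is right. Table 3 shows a place for scores, and nothing shows that the chosen wording is recorded. Exchanging 2 and 4 would introduce an error if raters had followed the headings.

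None of these removes the contradiction within the row.

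**Conclusion.** The point holds in limited form. The two middle anchors are misordered as printed. If the wording is followed, one improving change scores +2 instead of −2 and four others are mis-sized by 2 points, which can misclassify a patient when other items change as well.

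The misordering rests on the row's own score-6 anchor and needs no outside assumption. The 20% ceiling in step 3 assumes that the entry rule requires both primary symptoms and that breathlessness is one of the two secondary ones. The misclassification frequencies rest wholly on assumed distributions and should be read as an illustration, not as an estimate for this trial.

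A reader might infer that the total effective rate is invalid or biased towards one group. The documents do not support that: the effect depends on how raters scored, which is not shown. The primary eGFR endpoint and the sample size are unaffected.

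**What to change.** 1. Compare Table 3 with the source-language case report form and the rater instructions.
2. If only the article is wrong, correct the article.
3. If the case report form has the same order, exchange the two descriptors: 2 for breathlessness on moderate activity, 4 for breathlessness on mild activity.
4. In that case, establish before unblinding whether raters followed the wording or the mild, moderate and severe labels. Recode the item only if they followed the wording.
5. If this cannot be established, leave the recorded scores as they are and report a sensitivity analysis of the total effective rate without this item.

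The cost is one document check and a correction to one table row, with blinded recoding of one item or one extra analysis if needed. No change to sample size, visits or the primary analysis follows.

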## Background

Diabetic kidney disease (DKD), a chronic progressive disorder that is characterized by proteinuria and an irreversible decline in renal function, ultimately leads to end-stage renal disease (ESRD) in approximately 50% of patients in developed countries [1, 2]. DKD is one of the most important microvascular complications of diabetes, and its prevalence has increased dramatically worldwide in the past few decades [3, 4]. DKD accounts for approximately 20% of new dialysis prescriptions [5], and the high medical cost of renal dialysis treatment has created an urgent need for additional therapeutic strategies for DKD [6]. Comprehensive measures such as hypoglycemic and antihypertensive treatments have demonstrated beneficial effects in preventing the development of DKD, especially when used at the stage of microalbuminuria, and angiotensin-converting enzyme inhibitors (ACEIs) and angiotensin receptor II blockers (ARBs) reduce the risk of progression of DKD [7–9]. Losartan potassium, a classic angiotensin receptor blocker, is helpful in protecting the kidneys from damage in DKD [10]. In addition, this drug was recommended on the list of essential medicines of World Health Organization, which included the most effective and safe medications that experts consider necessary in a healthcare system. Treatment with losartan potassium may preserve some features of kidney structure and microalbuminuria due to its action on attenuating kidney fibrosis [11, 12]. However, combinations of traditional Chinese medicine (TCM) and Western medicine have advantages over Western medicine in delaying the progression of CKD and improving quality of life.

Keluoxin capsule (KLX) is a Chinese patent drug developed by the Chengdu Kanghong Pharmaceutical Co., Ltd. and Guang’anmen Hospital of the China Academy of Chinese Medical Sciences. KLX consists of six natural herbs: *Astragalus membranaceus*, *Ligustrum lucidum*, leech, rhubarb, Radix Pseudostellariae, and the fruit of the Chinese wolfberry (https://www.cnkh.com/product/17156.htm). KLX is used for DKD in patients with syndromes of qi and yin deficiency and blood stasis because it nourishes qi and yin, promotes blood circulation, and removes blood stasis. KLX was once named Tangshenping or Tangweikang [13, 14]. Research on KLX for DKD is included in the national Ninth Five-Year Plan project.

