### Outcome measures

#### Primary outcomes

The primary endpoint is the decline in the eGFR (ml/min/1.73 m^2^/year).

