### Statistics

#### Sample size

This study will be a trial of a new therapeutic regimen of KLX treatment. The sample size was calculated using software PASS based on a similar study on a Chinese herbal medicinal supplement conducted previously [20, 21]. According to the results of our previous trial, the mean decline of eGFR in the expected population was assumed to be 1.38 ± 3.21 and 2.61 ± 3.16 ml/min/1.73 m^2^/half a year in losartan potassium plus KLX versus losartan potassium plus placebo group, respectively. Therefore, we estimated that with a sample size of 105 patients assigned to each group (ratio 1:1) would be sufficient to achieve 90% power in detecting the differences of the primary endpoint based on a two-sided level of significance of 5%. Allowing for a 20% withdrawal rate, we plan to include 126 patients in this trial.

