Full Analysis Set (FAS), Per Protocol Set (PPS), and Safety Set (SS) are to be used for data analysis. According to intention-to-treat principle, FAS is defined as analysis of all cases who met all the inclusion criteria and none of the exclusion criteria, were randomized, and had at least one dose of the study drug. It included all enrolled and dropout cases except excluding participants. Multiple imputation analysis will be carried to explain the effect of missing data. Missing data of the primary outcomes will be carried forward with the principle of the last observation carried forward (LOCF). PPS includes the data from the subjects who follow the test protocol strictly, have good compliance, do not take the prohibited drugs during the test period, and complete the CRF form. SS refers to the participants who have made at least one visit and actual data recorded for safety indicators.

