To evaluate the effect of KLX, data were analyzed primarily using an intention-to-treat principle, and per-protocol analysis served as a supplement. For the primary outcomes, we will calculate the changes of eGFR from baseline. To compare the decline in eGFR between two groups, repeated-measures analysis of covariance model will be performed using baseline eGFR as covariates. Least-square means with SEMs and two-sided 95% CIs for differences between groups were estimated. For secondary outcomes, statistical description and comparison between groups will be performed according to whether the variables are continuous or categorical data. To be specific, the difference in classification indicators among secondary outcomes, including the incidence of Scr doubling, the incidence of ESRD, and the proportion of subjects with a progressive decline in eGFR of > 30% from baseline within 24 weeks, between groups will be compared using chi-squared or Fisher’s exact test. While the difference in the total effective rate of TCM syndrome scale scores between the two groups will be tested as rank data using Wilcoxon’s test or CMH test. Comparison of the continuous variables, such as the percent change in 24-h UTP and the change in UACR, will be performed applying independent *t* tests (or the Mann-Whitney *U* test). Safety evaluation is composed of comparison of parameters listed above as well as adverse events evaluation. Besides the detailed description, reason, and explanation of the adverse events, the chi-squared test or Fisher’s exact test will be used to compare the incidence of AEs between the two groups.

There will be no interim analysis of the data because there are no anticipated problems that are detrimental to the participants. All the data will be analyzed using Statistical Package for the Social Sciences (SPSS) version 17.0 (SPSS, Inc., Chicago, IL) software. All statistical tests will be two-sided, and significance will be considered for *p* values < 0.05.

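### LOCF for missing primary eGFR values freezes a decline the protocol expects to continue, so the group difference depends on who drops out and when

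*Protocol article*

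**What the plan says.** The protocol article, Data analyses, makes two statements on missing data. The first is general: "Multiple imputation analysis will be carried to explain the effect of missing data". It names no outcome and no role. The second is specific: "Missing data of the primary outcomes will be carried forward with the principle of the last observation carried forward (LOCF". The same section plans the primary comparison as follows: "repeated-measures analysis of covariance model will be performed using baseline eGFR as covariates". The full analysis set there requires only randomization, eligibility and one dose, and keeps dropouts.

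Other sections describe an outcome that keeps falling:
- Background calls the disease "a chronic progressive disorder that is characterized by proteinuria and an irreversible decline in renal function".
- Primary outcomes expresses the endpoint as a decline per year.
- Sample size states that "the mean decline of eGFR in the expected population was assumed to be 1.38 ± 3.21 and 2.61 ± 3.16" per half year, KLX first, and allows for 20% withdrawal.

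The Intervention section places visits at day 0 and weeks 4, 12 and 24.

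**The concern.** LOCF is neutral only if the outcome would have stayed where it was last seen. Here the protocol assumes the opposite in both groups. A patient who leaves after week 4 is recorded at week 24 with the small decline seen by week 4. A patient with only a baseline value, whom the full analysis set admits, is recorded with none. Leaving early therefore looks like preserved kidney function. The filled values also enter the model as if measured, so the standard error ignores that they are guesses.

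The sole primary estimate is at stake. If the groups lose patients alike, a real effect is diluted. If they do not, and KLX has no effect, the difference in dropout can pass for a renal benefit. Dropout may well be related to treatment or outcome. The Compliance section withdraws patients whose drug intake falls outside 80% to 120% of the prescribed amount. The Intervention section stops treatment at creatinine doubling or ESRD, although it does not say that eGFR measurement ends there. The Discussion itself lists poor compliance and dropout as remaining sources of bias.

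**Working it through.** **Inputs from the protocol.** Mean decline per half year 1.38 (SD 3.21) on KLX and 2.61 (SD 3.16) on placebo; 105 per group before and 126 after the withdrawal allowance; 20% withdrawal; visits at weeks 0, 4, 12 and 24. Difference = 2.61 − 1.38 = 1.23. Pooled SD = √((3.21² + 3.16²)/2) = 3.185.

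**Assumptions.** Decline is linear over 24 weeks; the carried value stands for week 24; the test compares the groups at week 24; 126 per group are analysed with SD 3.185. Dropout by group and its timing are not in the protocol and are varied.

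**The plan's own figure.** n = 2 × (1.960 + 1.282)² × 3.185² / 1.23² ≈ 141 per group for 90% power, two-sided 5%. The stated 105 gives about 80%. That is a separate matter, but it sets the right comparator for any statement about power.

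**Decline recorded under LOCF.** A patient last seen at week t is scored m × t/24 instead of m.

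| Last seen | KLX (true 1.38) | Placebo (true 2.61) |
|---|---|---|
| Week 0 | 0 | 0 |
| Week 4 | 0.23 | 0.435 |
| Week 12 | 0.69 | 1.305 |

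With a share p lost, the group mean becomes m × [1 − p × (1 − t/24)].

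**Planned effect, 20% lost in both groups at the same time.** The factor is 0.800, 0.833 or 0.900 for weeks 0, 4 and 12. The difference becomes 1.23 × 0.800 = 0.98, 1.23 × 0.833 = 1.03 or 1.23 × 0.900 = 1.11.

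**No effect, both groups decline 2.61.** False benefit for KLX = 2.61 × (1 − t/24) × (p_KLX − p_placebo). SE = 3.185 × √(2/126) = 0.401. Type I error = Φ(−1.96 + bias/SE) + Φ(−1.96 − bias/SE).

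| Loss, KLX v placebo | Last seen | False benefit | Type I error, about |
|---|---|---|---|
| 30% v 10% | Week 0 | 0.52 | 25% |
| 30% v 10% | Week 4 | 0.44 | 19% |
| 30% v 10% | Week 12 | 0.26 | 10% |
| 25% v 15% | Week 0 | 0.26 | 10% |
| 25% v 15% | Week 4 | 0.22 | 8% |
| 25% v 15% | Week 12 | 0.13 | 6% |
| 20% v 20%, same time | any | 0 | 5% |

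Timing alone is enough: with 20% lost in each group, KLX patients last seen at week 4 and placebo patients at week 12, the false benefit is 2.175 − 2.349 = −0.17 in decline, that is 0.17 in favour of KLX.

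**Planned effect, unequal loss at the same time.** The bias favours KLX only if p_KLX × 1.38 > p_placebo × 2.61, that is p_KLX/p_placebo > 2.61/1.38 = 1.89. Loss of 30% v 10% (ratio 3) gives 1.38, 1.36 and 1.31 for weeks 0, 4 and 12, above 1.23. Loss of 25% v 15% at week 4 (ratio 1.67) gives 1.19, below it. Loss of 10% v 30% gives 0.59, 0.69 and 0.91.

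**If the test averages over visits.** With no effect and 30% v 10% loss after week 4, the bias is 0 at week 4, (1.305 − 0.435) × 0.20 = 0.174 at week 12 and 0.435 at week 24. The average is 0.609/3 = 0.20.

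**The case against.** The strongest case for the plan is that LOCF is often conservative here. Under the planned effect, a lost placebo patient is spared more decline than a lost KLX patient, so equal or moderately unequal loss at equal times shrinks the difference. The protocol gives a single 20% withdrawal figure and nothing that predicts unequal loss. The largest false-positive figures need a threefold dropout ratio, no treatment effect and early exit. The protocol also names no contrast for the repeated-measures model, and an average over visits would roughly halve the week-4 figure. All of this stands. It limits the size and direction of the bias; it does not make the rule sound.

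Two stronger readings are tempting, and the document does not support them.

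- A reader might infer that LOCF pulls power from the planned 90% to about 79%, 72% or 69% (last seen week 12, week 4 or baseline, equal 20% loss). Most of that gap is not due to LOCF. Complete data on 105 per group give about 80%, and 126 × 0.80 ≈ 101 completers give about 78%. LOCF from week 12 therefore costs no power against completers. The 69% also keeps the SD at 3.185 although patients carried from baseline all have a change of exactly zero; with the resulting mixture variance it is about 75%.
- A reader might infer that the plan never says which method drives the primary result. It does: the LOCF sentence is tied to the primary outcome. Multiple imputation can be read as a sensitivity analysis, and its details may sit in an analysis plan that is not shown. That still leaves LOCF as the primary rule.

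**Conclusion.** The point holds as a bias in the primary estimate whose direction is conditional. The rule contradicts the protocol's own picture of the outcome, and 20% expected withdrawal gives it room to act. With equal loss it takes about 10% to 20% off a real effect (1.23 to between 1.11 and 0.98). With no true effect, more or earlier loss in one group creates a benefit for that group, and the type I error rises above 5% by an amount set by the dropout pattern.

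It would go too far to say that LOCF always favours the group that loses more patients. That is exact when the groups truly decline equally, which is the case that governs false positives. Under the planned effect with equal timing it fails unless KLX dropout exceeds about 1.9 times placebo dropout.

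The figures rest on linear decline, a week-24 comparison and assumed dropout splits. The qualitative point needs only continued decline and a carried value that stands for week 24. It would not apply in this form if each patient's rate were divided by that patient's own observed time, but the protocol does not say so.

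**What to change.** Before unblinding, make three changes to the Data analyses section:

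1. Remove LOCF from the primary analysis.
2. Fit the repeated-measures model already planned by likelihood to all observed eGFR values, with treatment, visit, treatment by visit, baseline eGFR and baseline by visit. Name the week-24 difference as the primary contrast. If data are missing at random and the model is correct, the expected difference stays at its true value (1.23 under the plan, 0 under no effect) whatever the dropout pattern.
3. Label the multiple imputation already named as the sensitivity analysis. Include a version in which dropouts from both groups continue to decline as in the placebo group, to test the missing-at-random assumption.

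The cost is wording and slightly more modelling work, with no new patients, visits or data. The primary analysis would then rely on missing at random, which is why the third change belongs with the second. The team should confirm that the software version named in the section can fit the model and the imputation, since the document does not show this.

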#### Exclusion criteria

A diagnosis of type 1 diabetes.A lack of diagnosed diabetic retinopathy.A history of simple renal hematuria or proteinuria with hematuria, sudden onset of edema and mass proteinuria without abnormal renal function, significant renal tubular dysfunction, coexisting renal tubular abnormalities, primary glomerulonephritis or secondary nephritis except DKD, or acute or chronic infection of the urinary system.A hemoglobin (HGB) concentration < 90 g/l.An ALB concentration < 30 g/l.A diagnosis of renal artery stenosis.A serum potassium concentration > 5.5 mmol/l.A serum creatinine (Scr) concentration ≥ 3 mg/dl (256 μmol/l).A history of severe cardiovascular or cerebrovascular disease within 3 months before screening.Severe systemic primary disease or dysfunction.Severe liver dysfunction or ALT or AST levels higher than 2.5 times the normal range.Hypertension treated with more than 3 types of antihypertensive drugs, blood pressure that is poorly controlled after administration of drugs with systolic blood pressure (SBP) ≥ 140 mmHg or diastolic blood pressure (DBP) ≥ 90 mmHg, or hypotension with SBP ≤ 90 mmHg or DBP ≤ 60 mmHg (resting position).Chronic (for more than 3 weeks) or recurrent diarrhea (where diarrhea is defined as elimination of increased volumes of thin fecal matter with increased frequency (> 3 times/day)).A history of active bleeding in the 3 months before screening.Coagulation disorders.Drug allergies or allergies to KLX or the active ingredient in losartan potassium.A history of alcohol or drug abuse or psychiatric disorders.Pregnancy, lactation, or plans to become pregnant during the trial.A history of enrollment in other clinical studies in the past 3 months.Other circumstances under which the investigators considered it inappropriate to participate in this clinical study.

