### Intervention

All investigators will be trained before the start of the study according to an investigators’ brochure. The enrolled patients with DKD will be asked to take losartan potassium tablets (50 mg per day) as the basic treatment and will also be administered KLX or placebo. The subjects in the treatment group will take four capsules of KLX orally thrice a day for 24 weeks. The participants in the control group will take the same amount of placebo for 24 weeks. Data from all the participants will be collected in four periods: on day 0 (V2), at 4 weeks ± 3 days (V3), at 12 weeks ± 5 days (V4), and at 24 weeks ± 5 days (V5).

KLX consists of six natural herbs: *Astragalus membranaceus*, *Ligustrum lucidum*, leech, rhubarb, Radix Pseudostellariae, and the fruit of the Chinese wolfberry. The placebo is identical in appearance and properties to KLX capsule without any active ingredient. Both KLX and the placebo will be manufactured by Chengdu Kanghong Pharmaceutical Co., Ltd., at a dose of 500 mg. The placebo, which will be identical in appearance and properties to KLX, will contain no active ingredients. The placebo will be verified by the quality control department and will meet the standards of placebo preparation. The interventions should stop for a given participant if the creatinine doubles or ESRD is detected. The participants will be asked to refrain from taking any other treatment for diabetic nephropathy, including ACEI or ARB drugs other than losartan potassium tablets and calcium hydroxybenzenesulfonate as well as Chinese medicine that affect evaluation of qi and yin deficiency and blood stasis syndrome during the trial.

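### Two analysis sets do not fit their stated purpose: the intention-to-treat FAS drops randomised, treated patients who breach an entry criterion, and the safety set requires an unspecified visit instead of a dose

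*Protocol article*

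**What the plan says.** All three analysis sets are defined in the Data analyses section of the protocol article.

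- **FAS.** It is introduced as following intention-to-treat, and then: "FAS is defined as analysis of all cases who met all the inclusion criteria and none of the exclusion criteria, were randomized". Members must also have "had at least one dose of the study drug". The next sentence reads: "It included all enrolled and dropout cases except excluding participants".
- **Role of the FAS.** For efficacy, "data were analyzed primarily using an intention-to-treat principle, and per-protocol analysis served as a supplement".
- **Safety set (SS).** "SS refers to the participants who have made at least one visit and actual data recorded for safety indicators". The definition contains no dosing condition.
- **Use of the SS.** The same section plans a chi-squared or Fisher's exact test of adverse event incidence between the two groups.

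Two other places bear on this. The Intervention section lists four data collection times: day 0 (V2) and weeks 4, 12 and 24 (V3 to V5). The Exclusion criteria end with an open clause: "Other circumstances under which the investigators considered it inappropriate to participate in this clinical study".

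**The concern.** An intention-to-treat analysis keeps patients in the arm to which they were randomised, so that the groups stay comparable. A FAS that requires every entry criterion to have been met permits removal after randomisation. Some of the criteria here are not purely objective: the TCM syndrome diagnosis and the investigator's open exclusion clause both need judgement. The primary comparison could then rest on a selected group while carrying an intention-to-treat label.

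A safety set should hold everyone exposed to the test product. This one is tied to a visit and to recorded safety data. Depending on which visit is meant, it can admit people who were never exposed or leave out people who were. In either case the adverse event rates compared between groups would not be rates among exposed patients.

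**Working it through.** The point concerns definitions, and the article states no figure for it that could be reproduced. I compared the texts first and then gauged the size with assumed inputs.

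**1. FAS: label against definition**

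| Patient (randomised) | Strict intention-to-treat | FAS as written |
|---|---|---|
| Eligible, dosed, completes | in | in |
| Eligible, dosed, drops out | in | in |
| Eligible, never dosed | in | out |
| Dosed, found to breach an entry criterion | in | **out** |

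The third row is a common and modest departure in a double-blind trial. The fourth row is the problem. The sentence that keeps dropouts but leaves out excluded participants points the same way, although it does not define who the excluded participants are.

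**2. SS: two readings of the visit condition**

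| Patient | Day 0 counts as a visit | Only visits after baseline count |
|---|---|---|
| Never dosed, day-0 safety data recorded | **in (wrong)** | out |
| Dosed, day-0 safety data recorded, leaves before week 4 | in | **out (wrong)** |

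The Intervention section includes day 0 among its four collection times, while the Study design section speaks of three visits. The article does not settle which reading applies. Each reading produces one error; no single reading produces both.

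**3. Size of the FAS problem (ineligible share assumed)**

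Inputs from the Sample size section: means 1.38 and 2.61, SDs 3.21 and 3.16, 126 per arm, two-sided 5%. Difference = 2.61 − 1.38 = 1.23. Pooled SD = √((3.21² + 3.16²)/2) = 3.185. Power comes from the noncentral t distribution with noncentrality 1.23 / (3.185 × √(2/n)) and assumes that everyone not removed is analysed.

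| Assumed share removed | Removed per arm | n per arm | Power |
|---|---|---|---|
| 0% | 0 | 126 | 86% |
| 2% | 2.5 | 123.5 | 86% |
| 5% | 6.3 | 119.7 | 85% |
| 10% | 12.6 | 113.4 | 83% |

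These levels do not match the article's stated 90%, which is a separate matter. Only the change down the column matters here, and it is small.

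**4. Size of the SS problem (counts assumed)**

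- *Day 0 counts.* If a share u of an arm was never dosed and had no events, an event rate r among the exposed is reported as r × (1 − u). With u = 5%, the reported rate is 0.95r.
- *Only later visits count.* Suppose k of 126 KLX patients and none of 126 placebo patients stop for an adverse event before week 4. The share omitted is k/126. Two-sided Fisher's exact p-values for those events taken alone are:

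| k | k/126 | p |
|---|---|---|
| 2 | 1.6% | 0.50 |
| 4 | 3.2% | 0.12 |
| 6 | 4.8% | 0.029 |

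Only a one-sided split of about 6 against 0 would by itself cross the 5% level. That is an extreme case.

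**The case against.** The FAS sentence may only describe the normal sequence of eligible, randomised, then dosed. The article does not say that eligibility is judged again after randomisation, and the open exclusion clause is written as a decision at entry. Participants, investigators, outcome assessors and analysts are blinded (Randomization, allocation concealment, and blinding; Data analyses), so a removal decided without knowledge of the arm has little scope to favour one arm. Dropping ineligible patients from a full analysis set can be acceptable when the criterion is objective, was measured before randomisation and is applied equally and blind in both arms.

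Much of this stands as a limit on the likely bias. It does not rescue the definition. The rule covers every criterion, states none of those conditions, and pairs eligibility with an explicit carve-out for excluded participants.

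For the SS, a reader might infer that the definition hides early adverse events and also admits unexposed patients. The documents do not support that combined claim, because the two harms need incompatible readings of the visit condition. Nor would an early event vanish. The Safety assessments section has detailed information on any adverse event recorded and events followed to resolution. The Data analyses section lists dropped and excluded cases as an item to analyse and asks for a detailed description of adverse events. At worst, and only if day 0 does not count, the patient leaves the formal incidence test. What remains is a missing dosing condition and an unspecified visit.

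It is also fair that an article condenses a longer protocol. But these are rules that the article states, not details that it leaves out.

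**Conclusion.** The concern holds as a mismatch between each set's purpose and its definition. It should be corrected, but it is moderate in weight.

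- **FAS.** The set that carries the primary analysis is not intention-to-treat as written, because it removes randomised, treated patients who breach an entry criterion. The consequence is possible selection after randomisation, limited by blinding, and not a material loss of power (about one percentage point if 5% per arm are removed). A reader might go further and infer that the exclusions will favour KLX; nothing in the article shows that.
- **SS.** Exposure is not required and the visit is not specified. Either never-dosed patients can enter the denominator, or dosed patients who leave before week 4 drop out of the formal comparison, depending on the reading.

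The wording faults are certain; their effect is not. The article gives no expected number of ineligible, never-dosed or early-leaving patients, so the 5% share and the 6-against-0 split are assumptions that illustrate scale only. The number affected may well be small.

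**What to change.** Redefine the two sets before unblinding.

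- **FAS:** all randomised patients who took at least one dose of KLX or placebo, analysed in the arm to which they were randomised. Delete the eligibility condition and the carve-out for excluded participants. Eligibility breaches exclude from the PPS only.
- **SS:** all patients who took at least one dose of KLX or placebo, analysed by treatment received. Count every reported adverse event, whether or not a later visit took place.
- **Dose:** name KLX or placebo explicitly in both definitions. The Discussion says that losartan is given to both groups from screening, so study drug alone could be read to include it.

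The cost is a wording change with no new data. The downside is that a few ineligible patients stay in the FAS and may slightly dilute the estimated effect; the supplementary per-protocol analysis would show how much that matters.
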